### Outcome measures and participant timeline

#### Outcome measures

Baseline dataDemographic data will be recorded using a general information questionnaire, which we designed in house. The questionnaire includes questions on age, gender, education, occupation, weight, and height.Clinical characteristics will be recorded using another in-house-designed questionnaire. Specifically, data will be collected on the surgery time, anesthesia time, intraoperative blood loss, intraoperative fluid transfusion volume, and vital signs (temperature, heart rate, respiratory rate, and blood pressure).Primary outcome measureThe primary outcome is the time to first passage of flatus—we will begin observing and recording when subjects return safely to the ward, and the subjects and their families will be asked to record the time of the first passage of flatus. The interval between the two time points will be then calculated.Secondary outcome measuresTime to first defecation: We will observe and record when the subjects return safely to the ward, and the subjects and their families will be asked to record the time of first defecation. The interval between the two time points will then be calculated.Abdominal pain: The subjects’ degree of postoperative pain will be assessed using the VAS scale [10]. The first evaluation will be performed 6 h after surgery, immediately before the first treatment. Evaluations will then be carried out once every 12 h, for seven evaluations. Assistance will be given to subjects and their families in recording this information.Abdominal distention: The Likert scale will be used to assess the subjects’ degree of postoperative abdominal distention [11]. The first evaluation will be performed 6 h after the surgery, immediately before the first treatment. Evaluations will then be carried out once every 12 h, for seven evaluations. Assistance will be given to subjects and their families in recording this data.Nausea: The VAS scale will be used to assess subjects’ degree of postoperative nausea [10]. The first evaluation will be performed 6 h after the surgery, immediately before the first treatment. Evaluations will then be carried out once every 12 h, for seven evaluations. Assistance will be given to subjects and their families in recording this data.Vomiting: The frequency of postoperative vomiting will be recorded. The first evaluation will be performed 6 h after the surgery, immediately before the first treatment. Evaluations will then be carried out once every 12 h, for seven evaluations. Assistance will be given to subjects and their families in recording this data.Mental status: The Hospital Anxiety and Depression Scale (HADS) will be used to assess the subjects’ postoperative mental status [12]. The HADS consists of 14 items: seven assess depression, and the other seven assess anxiety. The scores of the anxiety and depression subscales are classified as follows: 0–7 points indicate no symptoms, 8–10 points indicate suspected symptoms, and 11–21 points indicate confirmed symptoms. The first evaluation will be performed 24 h before surgery, and the second evaluation will be performed on the day of discharge.Quality of life: the Gastrointestinal Quality of Life Index (GIQLI) will be used in this study [13]. The GIQLI aims to measure the quality of life of subjects with digestive diseases and includes five domains: subjective symptoms, physiological functional status, daily life, social activities, and psychological and emotional state. Within these domains, 36 items are assessed, each with a score from 0 to 4 points, for a total possible score of 144 points. The normal population will score 12–125 points. The first evaluation will be performed 24 h before surgery, and the second will be conducted 2 weeks after discharge. A follow-up evaluation will be carried out 1 month after discharge. Higher scores indicate better health status.Safety indicatorsAn event can be defined as an adverse event if at least four subjects suffer a symptom—such as local skin allergies, dizziness, and low blood sugar—during the treatment-evaluation period. These events will be statistically analyzed, and treatment safety is evaluated on this basis, in accordance with the research protocol. If serious adverse events occur, they will be immediately reported and managed accordingly.Participant timelineFor a complete overview of the time schedule of enrollment, interventions, and assessment for participants, see Fig. 4.

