### Sample size estimation and statistical analysis

#### Sample size estimation

This study consists of two groups; the sample size-estimation formula is therefore based on a two-group, parallel, controlled design:$$ n=\frac{{\left({\mathrm{Z}}_{1-a/2}+{\mathrm{Z}}_{1-\beta}\right)}^2\times \left({\sigma}_1^2+{\sigma}_2^2\right)}{\delta^2}, $$where *n* represents the sample size in each group, σ represents the standard deviation, and *δ* represents the between-group difference with clinical significance. At an α value of 0.05, a power of 80 %, and given a two-sided test, we obtained Z scores of Z_1 − *a*/2_ = 1.96 and Z_1 − *β*_ = 0.84 from the Z score table. Eight subjects recruited from November 2015 to December 2015 were included in the pilot trial, and the primary outcome measure was the time to first flatus: *S*_1_ = 3.14 and *S*_2_ = 5.58. A decrease of 4 h in the time to first flatus was set as our clinical expectation based on preliminary tests and clinical experience. The above data were used to estimate the value of the overall parameter to be inserted into the above formula, and an n-value of 20.09 was obtained. Therefore, the rounded sample size in each group was 21; assuming a 15 % dropout rate, the final sample sizes in the experimental and control groups would be 25 cases, yielding the required 50 cases.

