#### Statistical analysis

Content of statistical analysisSample distribution: The absolute number of dropouts as well as the rate will be described for each data set. These data will be analyzed, and the reasons for each termination are listed in detail.Balance comparison: The subjects’ general information will be compared to assess the comparability of the two groups.Efficacy analysis: The subjects’ time to first passage of flatus will be used as the primary outcome measure to evaluate the efficacy and safety of APP in treating gastrointestinal dysfunction after laparoscopic cholecystectomy. The means and standard deviations will be calculated to describe the outcome measure, and the experimental and control groups will be statistically compared using two independent-sample *t* tests. The subjects’ time to first defecation, abdominal pain, abdominal distention, nausea, vomiting, mental status, and quality of life—i.e., the seven secondary outcome measures—will be used to evaluate the efficacy of the APP. Six of these—namely, the time to first defecation, abdominal pain, abdominal distention, nausea, vomiting, and quality of life—will be described using mean ± standard deviation. The scores for mental status will be recorded and categorized in terms of the classification criteria. The statistical analysis of time to first defecation is the same as that of time to first passage of flatus; abdominal pain, abdominal distention, nausea, vomiting, and quality of life will be statistically compared between groups using Repeated Measures Analysis of Variance (RMANOVA). However, before the RMANOVA is performed, a sphericity test will be used to determine whether the data are suitable for analysis using RMANOVA. If the data do not meet the conditions of sphericity, the correction factor *ε* will be used to correct the degree of freedom before the RMANOVA is performed. The categorical measure of mental status will be analyzed using either the rank-sum test or Spearman’s rank correlation.Safety analysis: In accordance with the above definitions of adverse events, we compiled a list describing, grading, and explaining the adverse events in detail. We will ascertain descriptive statistics of the absolute number—as well as the incidence—of each adverse event in both groups. When making comparisons, we will use the *χ*^2^ test or Fisher’s exact test for statistical analysis.Methods of statistical analysisData will be analyzed in accordance with the principle of intention-to-treat (ITT). That is, we will include all subjects who were treated at least once in the trial. Efficacy and safety measures will be analyzed in accordance with “per-protocol” (PP), whereby we will include all subjects who completed the entire trial and followed the protocol requirements. Quantitative variables in the trial data will be expressed as $$ \overline{\mathrm{X}}\pm \mathrm{S}\mathrm{D} $$ for statistical description, whereas qualitative variables will be recorded as the number of cases in each category. If the quantitative variables constitute repeated measures data, then RMANOVA will be used for comparison, and the sphericity test will be used to determine the suitability of, as well as to correct, the data. Qualitative variables will be analyzed using either the rank-sum test or Spearman’s rank correlation; count data for incidence will be compared using the *χ*^2^ test or Fisher’s exact test. All statistical tests are two-sided, and differences with *P* values < 0.05 will be considered statistically significant. Statistical analysis will be performed using SPSS 19.0 statistical software for calculations.

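### The HADS scores are cut to three bands before testing and no stated analysis uses the preoperative score, so the planned comparison of mental status is valid but inefficient

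*Protocol article*

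**What the plan says.** All references are to the protocol article.

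- Under Outcome measures, HADS has a seven-item anxiety subscale and a seven-item depression subscale. Each is banded: "0–7 points indicate no symptoms, 8–10 points indicate suspected symptoms, and 11–21 points indicate confirmed symptoms". On timing: "The first evaluation will be performed 24 h before surgery, and the second evaluation will be performed on the day of discharge".
- Under Statistical analysis, in the efficacy paragraph: "The scores for mental status will be recorded and categorized in terms of the classification criteria". Then: "The categorical measure of mental status will be analyzed using either the rank-sum test or" Spearman's rank correlation.
- The same paragraph keeps the other six secondary outcomes on their numeric scale. Besides time to first defecation, "abdominal pain, abdominal distention, nausea, vomiting, and quality of life—will be described using mean ± standard deviation". Those five are also tested as numbers: "abdominal pain, abdominal distention, nausea, vomiting, and quality of life will be statistically compared between groups using Repeated Measures Analysis of Variance".
- GIQLI, the quality-of-life score, also has an assessment 24 h before surgery, so the plan treats two questionnaire scores with a preoperative value differently and gives no reason.
- The significance rule is general: "All statistical tests are two-sided, and differences with *P* values < 0.05 will be considered statistically significant".

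**The concern.** Three features of the stated analysis reduce what it can show.

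1. **Banding.** A fall from 7 to 1, or from 20 to 12, leaves a patient in the same band. A fall from 8 to 7 moves the patient to a better one. Most of the movement on a 22-point scale can therefore be invisible to the test.
2. **No stated use of the preoperative score.** A patient's anxiety before surgery is likely to predict anxiety at discharge. With 21 to 25 patients per arm, a chance imbalance at baseline can be sizeable. Adjustment would deal with it and reduce residual variance at no cost.
3. **Spearman's correlation as an alternative.** The text does not say which two variables would be correlated, and a correlation coefficient is not a between-arm difference in HADS points.

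The Discussion presents anxiety and depression as secondary indicators of recovery. At stake is whether the trial can detect a change in them and state its size on the scale that was measured.

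**Working it through.** **Step 1. The plan's own figure, to fix the number per arm.** Inputs from Sample size estimation: z values 1.96 and 0.84, SDs 3.14 and 5.58, difference 4 h.

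n = (1.96 + 0.84)² × (3.14² + 5.58²) / 4² = 7.84 × 40.996 / 16 = 20.09, rounded up to 21 per arm. Then 21 / 0.85 = 24.7, rounded up to 25 per arm, 50 in total.

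The stated figures reproduce. They concern time to first flatus only; the article gives no power figure for HADS. The planned number of evaluable patients is 21 per arm, so that number is used below.

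**Step 2. Information kept by three bands.** The article gives no HADS distribution, so a normal score with SD 3.5 is assumed. With cuts at 7.5 and 10.5, the largest share of the raw-score information that three ordered bands can keep is

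Σ (difference in φ between the band's limits)² / (probability of the band).

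For an assumed mean of 6, the cuts are (7.5 − 6)/3.5 = 0.429 and (10.5 − 6)/3.5 = 1.286. The band probabilities are about 0.67, 0.23 and 0.10, and φ at the cuts is 0.364 and 0.175. The three terms are about 0.199, 0.153 and 0.307, which sum to 0.66. Repeating this:

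| Assumed mean | Share kept by the bands |
|---|---|
| 4 | 46% |
| 6 | 66% |
| 8 or 10 | 78% |

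Relative to a baseline-adjusted analysis, the share is multiplied by (1 − ρ²), where ρ is the pre-post correlation. At mean 6 this is 0.66 × 0.91 = 0.60 for ρ = 0.3 and 0.66 × 0.51 = 0.34 for ρ = 0.7.

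**Step 3. Power by simulation.** Scores were rounded, clipped to 0–21 and tested two-sided at 0.05. Assumptions, none from the article: SD 3.5, shift 0.6 SD (0.6 × 3.5 = 2.1 points), 21 per arm. Individual settings:

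| Mean | ρ | Rank-sum on bands | Rank-sum on raw score | ANCOVA on raw score |
|---|---|---|---|---|
| 6 | 0.6 | 27% | 44% | 61% |
| 8 | 0.6 | 37% | 46% | 64% |
| 10 | 0.6 | 39% | 45% | 65% |
| 10 | 0.3 | 39% | 45% | 50% |

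Over means 5–10 and ρ 0.3–0.6 the ranges are about 21–40%, 43–46% and 48–64%; simulation error is about a point. In the rows above, banding costs 44 − 27 = 17, 46 − 37 = 9 and 45 − 39 = 6 points. Over the whole range it costs about 6–24 points, most at the lowest mean, where most patients fall in the 0–7 band. Baseline adjustment adds a further 61 − 44 = 17 points at mean 6, ρ = 0.6, but only 50 − 45 = 5 points at mean 10, ρ = 0.3.

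**Step 4. Other assumptions.** With a shift of 0.8 SD, 21 per arm, means 4–10 and ρ 0.3–0.7, the bands give 23–62% and ANCOVA 71–94%. With a shift of only 0.3 SD, 25 per arm, mean 6 and ρ = 0.6, the three methods give 13%, 17% and 24%. The ordering is the same throughout.

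**Step 5. Validity.** With no true difference (25 per arm, mean 6, ρ = 0.6), type I error is near 5% for all three methods.

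**Step 6. Rank-sum against Spearman.** If Spearman's coefficient is taken between arm and band, its power is within about 2 points of the rank-sum test in every setting run.

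**The case against.** The strongest defence is that the planned test is sound. The cut-points are prespecified and belong to the scale, type I error is held, and raw scores are recorded, so nothing is lost for good. HADS is one of seven secondary outcomes in a trial that calls itself a pilot. Covariate adjustment is often left to an analysis plan that is not shown here, and every input to the power figures is assumed. For a small effect no method has adequate power, and at means of 8 to 10 banding alone costs only about 6 to 9 points.

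Much of this stands, and it limits the point to one of efficiency. It does not remove it. The article does not leave the analysis of HADS open: it chooses to band the scores and names the tests for the bands, and a later plan that followed it would inherit the loss. The direction of the loss does not depend on the assumptions, only its size.

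A reader might infer four stronger things that the article does not support.

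- *That the preoperative score will be discarded.* The article does not say so. It only assigns that score no role in any stated comparison.
- *That the choice between two tests allows a favourable result to be picked.* For arm against band, the two tests almost always agree, and the statisticians are to be blinded to group. What remains is an undefined correlation and the wrong kind of estimate.
- *That no effect measure results.* Counts per category are to be reported, which give a crude one.
- *That ranks will be applied to gender or occupation.* The general sentence on qualitative variables is loosely worded, but the balance comparison names no test.

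**Conclusion.** The point holds as one of inefficiency on a secondary outcome. The article fixes an analysis of banded HADS scores, gives the preoperative score no stated use, and treats quality of life, which has the same kind of baseline, as a score.

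Under the main assumptions (SD 3.5, shift 0.6 SD, mean 5–10, pre-post correlation 0.3–0.6), the planned test with the 21 evaluable patients per arm has roughly 21–40% power, against 48–64% for a baseline-adjusted score. Power at 25 per arm would be higher for every method, but 25 is the number randomised, so it would flatter the figures. None of the HADS values comes from the article, so the sizes are illustrative; the ordering held in every setting tried.

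The analysis of time to first flatus and the sample size of 50 are not affected.

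**What to change.** In the efficacy paragraph of Statistical analysis, replace the sentences on mental status with the following content:

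- The HADS anxiety and depression scores (each 0–21) at discharge are analysed separately by ANCOVA, with treatment group as factor and the score taken 24 h before surgery as covariate.
- The adjusted difference between groups in HADS points is reported with its 95% CI.
- Numbers of patients in the bands 0–7, 8–10 and 11–21 are shown by group and time point as description only.
- The Spearman option is deleted for mental status, both here and where the general methods paragraph repeats it.

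Both HADS assessments are already scheduled and the scores are already recorded, so no visit, form or sample-size change is needed. The cost is a change of wording in the statistical section, made and dated before any unblinded analysis. Recruitment was still under way when the article was written.

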#### Elimination criteria

Subjects will be removed from the study if they (1) switch to laparotomy; (2) refuse to continue this treatment after inclusion, regardless of the reason; (3) experience serious complications during treatment (e.g., peritonitis or biliary fistula); (4) are transferred for other specialist treatment, became comatose, or die; (5) cannot attend follow-up visits, for whatever reason; (6) do not meet the inclusion criteria but were included by mistake; or (7) show poor clinical compliance (failure to adhere to the treatment protocol or to provide complete information), which may have affected the efficacy and safety of the treatment.

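### The plan declares intention-to-treat, then assigns efficacy and safety to a completers-only per-protocol set, and does not say which is primary

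*Protocol article*

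**What the plan says.** All of this is in the protocol article.

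- **Statistical analysis, methods.** Intention-to-treat is named as the principle and explained so: "That is, we will include all subjects who were treated at least once in the trial". The next sentence reads "Efficacy and safety measures will be analyzed in accordance with" per-protocol, "whereby we will include all subjects who completed the entire trial and followed the protocol requirements". Per-protocol is not called secondary, supportive or additional.
- **Elimination criteria.** Subjects are removed from the study after inclusion if, among other reasons, they "refuse to continue this treatment after inclusion, regardless of the reason"; "experience serious complications during treatment (e.g., peritonitis or biliary fistula"); "are transferred for other specialist treatment, became comatose, or die"; "cannot attend follow-up visits, for whatever reason"; or comply poorly, which includes not giving complete information.
- **Outcome measures.** The primary outcome, time to first flatus, is recorded from return to the ward. The quality-of-life questionnaire (GIQLI) is repeated 2 weeks and 1 month after discharge.
- **Statistical analysis, content.** Dropouts are counted per data set, with reasons. Adverse-event incidence is compared between groups by a chi-square or Fisher test.

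**The concern.** Efficacy and safety are the only two classes of outcome in the plan. If both go to the per-protocol set, the intention-to-treat set is left with no outcome to analyse, and the declared principle has no effect.

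Membership of the per-protocol set is decided after randomisation. Refusal, complications, transfer and poor compliance may each depend on the arm or on how slowly the patient recovers. A comparison restricted in this way no longer has the protection of randomisation.

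Two consequences follow from the literal text. A patient whose first flatus was fully recorded in hospital can leave the primary comparison for missing a questionnaire visit weeks later. And patients with serious complications during treatment, or who die, are by definition outside the set in which adverse events are compared.

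If instead two parallel analyses are intended, the order between them is missing. With P < 0.05 as the criterion, the set that carries the conclusion could then be chosen after the results are known.

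**Working it through.** **1. The two sets side by side.**

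| Patient | Treated-at-least-once set | Per-protocol set |
|---|---|---|
| Randomised, never treated | out | out |
| Refuses after the first session | in | out |
| Serious complication, transfer, coma or death after the first session | in | out |
| Flatus time recorded, later follow-up visit missed | in | out |
| Poor compliance | in | out |

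The sets differ for every kind of patient removed after the first session, so the choice between them matters. Neither set is all randomised patients.

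**2. The plan's own sample size** (Sample size estimation; SDs 3.14 and 5.58, difference 4 h, z-values 1.96 and 0.84).

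n = (1.96 + 0.84)² × (3.14² + 5.58²) / 4² = 7.84 × 40.996 / 16 = 20.09, rounded up to 21. Allowing 15% dropout, 21 / 0.85 = 24.7, so 25 per arm and 50 in total. The stated figures reproduce. The plan thus expects to lose about 25 − 21 = 4 patients per arm.

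**3. What removal could do to the primary comparison.** The document does not say how removals relate to outcome, so these are assumed scenarios: normal data, no true effect, common SD √((3.14² + 5.58²)/2) = 4.53 h, 25 per arm, and a t test on those who remain, by simulation.

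| Removed | Difference created between arms | Type I error |
|---|---|---|
| 4 per arm at random | about 0 h | about 5% |
| Slowest 1 in one arm, 1 at random in the other | about 0.37 h | about 7% |
| Slowest 2 in one arm, 2 at random in the other | about 0.69 h | about 9% |
| Slowest 3 in one arm, 3 at random in the other | about 0.98 h | about 13% |
| 4 from the slower half of one arm, none in the other | about 0.64 h | about 7% |
| Slowest 4 in one arm, none in the other | about 1.25 h | about 18% |
| Slowest 4 in both arms | about 0 h | about 9% |

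The 1.25 h shift is 1.25 / 4 = 31% of the 4 h target. The shift scales with the SD of the arm affected. For the slowest 3 it is 0.98 × 3.14 / 4.53 = 0.68 h if that is the acupressure arm, and 0.98 × 5.58 / 4.53 = 1.2 h if it is the sham arm. Loss of slow patients from the acupressure arm favours acupressure; loss from the sham arm works against it.

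**4. Safety, with assumed counts.** Suppose 4 of 25 against 0 of 25 treated patients have a serious complication (Fisher P = 0.11). If those 4 are eliminated, the per-protocol table shows 0 of 21 against 0 of 25 (P = 1.0).

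**The case against.** The strongest reply is that the article condenses a longer protocol and simply names two sets to be run side by side. The first sentence applies intention-to-treat to the data without limit, and dropouts are to be described per data set, which implies more than one. On that reading the patient with a missed questionnaire visit stays in one of the analyses. This stands as a possible intention, so a reader who infers that per-protocol is certainly the only analysis goes further than the text. It does not remove the defect: the article does state the sets, gives efficacy and safety to per-protocol, and ranks neither.

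Three other strong readings are not supported.

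- **That the primary result will be biased.** Random loss gives no bias, and the document gives no information on which patients will be lost or from which arm. The larger figures above come close to a worst case.
- **That the safety result must look clean, or that deaths and serious complications vanish.** The symptoms named under Safety indicators (skin allergy, dizziness, low blood sugar) are not themselves reasons for elimination, so a patient who has one and finishes stays in. Termination reasons are listed, serious adverse events are reported at once, and adverse-event records are monitored. What is lost is the place of the eliminated patients in the between-group comparison.
- **That the trial loses its planned power.** With the plan's SDs and a t test, power is 79.8% with 21 per arm and 86.4% with 25. The sample size was inflated so that about 80% would remain after dropout.

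Calling a treated-at-least-once set intention-to-treat is, taken alone, mainly a labelling fault. The document gives no figure for patients randomised but never treated.

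**Conclusion.** The point holds as an internal contradiction in the Statistical analysis section, made consequential by the Elimination criteria. Followed as written, it removes patients after randomisation from the primary comparison, including some whose primary outcome was recorded, and removes the seriously ill from the comparative safety analysis. It can bias the result if removal is related to arm and outcome. Neither the size nor the direction can be derived from the document, and the range of about 7% to 18% for type I error rests wholly on assumed one-arm loss of the slowest patients.

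The contradiction itself needs no assumption. Because it governs both the primary and the safety conclusions, it should be resolved before analysis; the article reports recruitment as ongoing. The pilot label does not excuse it, since the trial is powered for a hypothesis test and is meant to provide evidence for promoting the therapy.

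**What to change.** Amend the Statistical analysis section and the Elimination criteria to state that:

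- the primary and secondary efficacy analyses include all randomised patients in the arm assigned, using every recorded outcome;
- the per-protocol analysis is a sensitivity analysis only;
- for analysis, the elimination list only defines the per-protocol set and does not delete data already recorded;
- safety is analysed in all patients who received at least one session.

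The sample size stays at 50, and no extra patients or visits are needed. The cost is wording and, possibly, a slightly smaller estimated effect than the per-protocol set would give.
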